## Abstract

**Background:**

The Pre-Consultation Educational Group Intervention pilot study seeks to assess the feasibility and inform the optimal design for a definitive randomized controlled trial that aims to improve the quality of decision-making in postmastectomy breast reconstruction patients.

**Methods/design:**

This is a mixed-methods pilot feasibility randomized controlled trial that will follow a single-center, 1:1 allocation, two-arm parallel group superiority design.

Setting: The University Health Network, a tertiary care cancer center in Toronto, Canada.

Participants: Adult women referred to one of three plastic and reconstructive surgeons for delayed breast reconstruction or prophylactic mastectomy with immediate breast reconstruction.

Intervention: We designed a multi-disciplinary educational group workshop that incorporates the key components of shared decision-making, decision-support, and psychosocial support for cancer survivors prior to the initial surgical consult. The intervention consists of didactic lectures by a plastic surgeon and nurse specialist on breast reconstruction choices, pre- and postoperative care; a value-clarification exercise led by a social worker; and discussions with a breast reconstruction patient.

Control: Usual care includes access to an informational booklet, website, and patient volunteer if desired.

Outcomes: Expected pilot outcomes include feasibility, recruitment, and retention targets. Acceptability of intervention and full trial outcomes will be established through qualitative interviews. Trial outcomes will include decision-quality measures, patient-reported outcomes, and service outcomes, and the treatment effect estimate and variability will be used to inform the sample size calculation for a full trial.

**Discussion:**

Our pilot study seeks to identify the (1) feasibility, acceptability, and design of a definitive RCT and (2) the optimal content and delivery of our proposed educational group intervention. Thirty patients have been recruited to date (8 April 2013), of whom 15 have been randomized to one of three decision support workshops. The trial will close as planned in May 2013.

**Trial registration:**

NCT01857882

## Background

Women with a history of breast cancer now constitute the largest group of cancer survivors [1], with over 85% surviving for greater than 5 years after diagnosis [2]. Mastectomy remains a common form of breast cancer treatment, with 37% of American women undergoing mastectomy as their definitive cancer treatment in 2006 [3]. The goal of breast reconstruction is to reconstruct a mastectomy defect without affecting cancer outcomes [4]. The opportunity to restore the breast mound through reconstructive surgery has been shown to enhance a woman’s self-image and femininity [5-7], as well as provide psychosocial benefit [8].

The majority of women who undergo breast reconstruction are satisfied with the outcome and the aesthetic result [5,9-11]. However, one fourth of women report being dissatisfied with some component of their cancer or reconstructive care [12]. Failure of the physician to provide adequate information about treatment options is the most frequent source of cancer patient dissatisfaction [13], and breast reconstruction patients have expressed a need for further information regarding the complex decision to pursue breast reconstruction [14-16]. Information dissatisfaction and a mismatch between a patients’ preferred and actual role in decision-making may contribute to decision regret in breast oncology patients [12,17-19]. Implementation of strategies to incorporate shared decision-making can improve the quality of treatment decisions [20]. Developing the self-confidence to make and express a treatment decision (defined as decision self-efficacy [21]) is a necessary component of shared-decision making, and this attribute can be enhanced through decision support interventions [22].

Given the financial and time constraints that exist in our current health-care system, it is not feasible to relay detailed information regarding every aspect of breast reconstruction during a single patient consultation. In addition, the breast reconstruction discussions can be highly complex, as there are many different techniques (implant vs. autologous tissue, one-stage vs. two-stage), timing (delayed vs. immediate), and complications that are unique to each procedure [4,23]. In such scenarios of complex medical decision-making, decision support techniques may be an effective solution to information provision [13] and shared decision-making [14,24]. As a result, we developed a pre-consultation educational group intervention delivered in a group setting for women considering breast reconstruction, with the aims to fill an existing information-gap, promote high-quality decision-making, and enhance decision self-efficacy. This pilot study will be the first step in the evaluation of our educational group intervention, and the results will be used to determine the feasibility and inform the optimal design for a definitive randomized controlled trial. Figure 1 shows a pre- and postoperative photo of a patient who underwent delayed breast reconstruction using autologous tissue reconstruction.

**Figure 1 F1:**
[figure not shown]
**Delayed breast reconstruction. (A)** Preoperative photograph demonstrating right mastectomy defect after post-mastectomy radiation. **(B)** Postoperative photograph after delayed breast reconstruction using autologous tissue reconstruction.

### Hypothesis

Patients seeking consultation for breast reconstruction allocated to the pre-consultation educational group intervention plus usual care will have greater decision self-efficacy, satisfaction with information, decision preference, and decision choice, perceived involvement in care, breast reconstruction knowledge, and less decisional conflict as measured approximately 1 week after intervention and surgical consultation compared with patients allocated to receive usual care alone.

### Pilot study objectives

1. To determine feasibility and acceptability of randomization, intervention uptake, and data collection

2. To assess implementation and fidelity of the outcome measures and intervention

3. To pilot trial procedures including recruitment (giving information and obtaining preliminary consent via telephone recruitment), randomization, intervention delivery (workshop scheduled same day as initial surgical consult), and outcome measurement (mailed questionnaires)

4. To use qualitative research methods to assess the content and acceptability of the intervention and learn from patient interviews how to improve the delivery of the intervention for the full trial

5. To obtain estimates of variance and a preliminary estimate of the effect of the intervention on preliminary trial outcomes (decision self-efficacy, satisfaction with information, decision preference and decision choice, decisional conflict) and service outcomes such as duration of consultation.

## Methods/design

This is a mixed-methods pilot feasibility randomized controlled trial that will follow a single-center, 1:1 allocation, two-arm parallel group superiority design. The study setting will be the University Health Network (UHN), a tertiary care cancer center in Toronto, Canada, with three plastic and reconstructive surgeons who specialize in breast reconstruction. Research ethics board approval was obtained from the University Health Network (11-1027-CE).

### Participants

Adult women referred to one of the plastic surgeons for consideration of breast reconstruction will be eligible to participate. The study coordinator is responsible for identification and recruitment of potentially eligible participants. Because the intervention (educational workshop) will occur *before* the initial surgical consultation, it is necessary to identify subjects from faxed referrals and determine their eligibility via telephone confirmation at the time of recruitment and prior to the initial surgical consultation. Participants will be excluded if they are referred for reconstruction after atypical breast malignancy (e.g., angiosarcoma) or metastatic breast cancer, secondary breast reconstruction, have cognitive impairment or uncontrolled psychiatric diagnosis, or cannot read or write in English. Once eligibility has been confirmed with the study coordinator, subjects who indicate an interest in participation will be enrolled after providing informed consent over the telephone, and study packages will subsequently be mailed. Participants will be officially registered upon receipt of signed consent through return mail. Baseline measures (T0) will be assessed prior to randomization and returned in postage-paid envelopes. Participants in the study and control groups will complete T1 measures approximately 1 week after the initial surgical consultation. The participant timeline is outlined in Figure 2.

**Figure 2 F2:**
[figure not shown]
Study design flowchart and participant timeline.

### Randomization and allocation of interventions

Once informed consent has been obtained from each participant and the baseline questionnaire returned by mail, the next opaque, sealed envelope in sequence will be opened by the study coordinator to determine the participant’s randomized treatment allocation. A computer-generated random allocation sequence will be created and sealed in opaque envelopes by the program biostatistician independent form the study coordinator with 1:1 allocation to the educational group intervention or usual care and balanced in blocks of ten.

### Intervention

Patients in the experimental group will participate in a pre-consultation educational group intervention in addition to receiving usual care. The intervention will be 2 h in duration on the morning of the consultation and will be facilitated by a dedicated social worker from psycho-oncology. Concerning the workshop development and structure, the intervention will incorporate the key components of shared decision-making (patient-physician involvement, shared information, expression of preferences) [13] and decision support (information provision, values clarification and patient involvement) [25-27] with the philosophy of delivering supportive care to cancer patients [28-30].

•Surgeon – 30 min: treatment options for breast reconstruction with indications/contraindications, advantages/disadvantages, expected postoperative course, aesthetic result (realistic photos), and complications with probabilities

•Registered nurse – 30 min: preparing for surgery, postoperative recovery, and how to navigate the health-care system

•Social worker (SW) – 30 min: values clarification exercise (Figure 3)

•Breast reconstruction patient volunteer: 30 min: questions and answers about her personal experience

**Figure 3 F3:**
[figure not shown]
**Values clarification exercise.** The last component of the Pre-Consultation Educational Group Intervention is the values clarification exercise. Using an interactive example, the purpose of the values clarification exercise is explained, and patients are invited to consider their personal values and complete the exercise. This is brought to the surgical consultation to incorporate patient values into the shared decision-making process.

Patients in the experimental and control group will receive usual care. At the UHN, all patients are asked to read a breast reconstruction information booklet and visit the website developed by the group prior to their consultation with the plastic surgeons. They are then booked for a 45-min consultation with a consultant plastic surgeon and a surgical resident or fellow. A thorough history and physical exam are performed, and specific information regarding reconstruction options, advantages, and complications is provided, followed by a discussion about patient preferences. In addition, all patients are referred to speak with a volunteer patient at a later date if desired. Appointments will be scheduled in batches to prevent contamination between those randomized to the experimental and control groups.

### Outcome measures

#### Pilot and feasibility outcome measures

*Feasibility and acceptability of randomization, treatment allocation, and data-collection procedures:* Recruitment and attrition rates will be recorded. We will measure the proportion of participants that submits *complete* primary and secondary outcome measures and baseline questionnaires. *Treatment Implementation and fidelity:* We will record the proportion of participants who received their randomly allocated treatment assignment to monitor participant adherence to treatment allocation. *Acceptability of interventions, assessment of primary outcome, and refinement of the educational group intervention content and delivery:* A subgroup of participants allocated to both the experimental and usual care groups will be asked to participate in a brief qualitative telephone interview. Purposeful sampling will be used to recruit five patients from each group to achieve data saturation and variability [31]. Telephone interviews will be conducted by a social worker trained in qualitative methods after the decision regarding breast reconstruction has been made, which we consider to be when a patient signs the surgical consent. All participants randomized to the workshop will additionally be asked to complete a written survey for evaluation of the intervention immediately after participation in the workshop.

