2) The BREAST-Q is a procedure-specific and validated PRO that measures Hr-QOL and patient satisfaction with PMBR [36-39]. The “Satisfaction with Information” Subscale specifically measures patient satisfaction with the preoperative information and care provided by the plastic surgeon and other members of the medical team. There are 15 items that use a four-level Likert scale response format; the score is transformed on a scale of 0 to 100 with higher scores indicating greater satisfaction [36-39].

*Service outcomes* will be measured using the uptake rate of breast reconstruction, consultation length, number of consultations until a decision is made (consent signed), the physician satisfaction scale [40], and a breast reconstruction knowledge test [41].

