### Interpretation of pilot results

Feasibility targets include ≥ 60% recruitment, ≥ 80% retention after randomized treatment assignment, and ≥ 80% completion of primary outcome measure. Success will also be measured based on high treatment fidelity measured through observation of the intervention and participant qualitative report. To inform our decision for the primary outcome for a definitive RCT, the most important outcome measure for patients will be solicited and ascertained through qualitative methods.

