## Discussion

To reduce unnecessary variation in treatment and improve quality of cancer care among breast cancer patients, there has been a growing interest in engaging patients through the decision-making process [48,49]. Particularly for breast reconstruction there is a paucity of studies designed to address patients’ unique informational and supportive-care needs, and there has been a call to action to develop and implement interventions that enhance patient empowerment [50]. Only one RCT has designed and implemented a decision support intervention for patients considering breast reconstruction [51]. While patients assigned to the pre-consultation computer-based decision support intervention demonstrated greater knowledge scores, outcomes related to shared decision-making or decision quality were not assessed using validated instruments [51]. Retrospective observational studies from single institutions suggest that well-informed patients already participate in the decision whether or not to undergo breast reconstruction [12,41], but interventions can improve involvement and satisfaction for the decision regarding the type of reconstruction (implant-based or autologous tissue reconstruction) among women who decided to have breast reconstruction [52]. However, inferences regarding the utility of decision-support interventions for breast reconstruction patients from non-randomized and particularly retrospective studies must be made with caution. Furthermore, no study has examined the potential of group workshops to enhance patient engagement and decision quality; educational interventions delivered in a group setting have been demonstrated to be an effective tool to address informational and psychosocial needs for breast cancer survivors [30]. Therefore, we designed a novel intervention to address identified gaps in care to promote shared decision-making and improve the quality of patient decisions surrounding breast reconstruction.

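### Defining the reconstruction decision only as signed surgical consent leaves women who decline or defer outside the interview frame and without a consultations-to-decision count

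*Protocol article*

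**What the plan says.** The protocol article fixes the decision event in two places.

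- *Pilot and feasibility outcome measures*: the telephone interviews take place "after the decision regarding breast reconstruction has been made, which we consider to be when a patient signs the surgical consent". On sampling, the same paragraph states: "Purposeful sampling will be used to recruit five patients from each group to achieve data saturation and variability".
- *Trial outcome measures*, service outcomes: one of the five outcomes listed is the "number of consultations until a decision is made (consent signed".

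Both measures feed later decisions. Objective 4 uses the interviews to judge the workshop's content and acceptability and to improve its delivery. *Interpretation of pilot results* adds that, to help choose the definitive trial's primary outcome, "the most important outcome measure for patients will be solicited and ascertained through qualitative methods". Objective 5 is "To obtain estimates of variance and a preliminary estimate of the effect of the intervention on preliminary trial outcomes", and it extends to service outcomes, with consultation duration as its example.

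Elsewhere the article treats reconstruction as an open question. Under *Participants*: "Adult women referred to one of the plastic surgeons for consideration of breast reconstruction will be eligible to participate". Among the service outcomes is the "uptake rate of breast reconstruction". The *Discussion*, summarizing earlier observational work, refers to "the decision whether or not to undergo breast reconstruction".

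**The concern.** Only women who choose surgery sign a surgical consent. In a decision-support trial, an informed choice not to have reconstruction is also a decision, and the workshop could plausibly make it more or less common. A rule that recognizes only the signature leaves that choice with no endpoint.

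Two things are at stake. The interviews would draw on women who went ahead, so the views of those whom the workshop helped to decline, or left undecided, would be missing from the material used to revise the workshop and to choose the primary outcome. The consultation count would be compared between arms only among signers, a group formed after randomization.

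**Working it through.** **Step 1: apply the rule to each possible status.** The plan states no figure on this point, so there is none to reproduce. The check is to read the definition against each course a participant can take.

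| Status | Decision made, as defined | Due for interview | Consultation count |
|---|---|---|---|
| Signs | yes | yes | defined |
| Declines | never | never | no endpoint |
| Defers, later signs | only on signing | only then | defined only then |
| Still undecided | no | no | none yet |

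The second row conflicts with eligibility (women still considering reconstruction), with uptake as an outcome (which anticipates that some will not proceed) and with the *Discussion*, which treats the decision as one that can go either way. The rule is stated explicitly, twice, so this is not a detail that the article merely leaves out.

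**Step 2: how many women would have no count.** Inputs: about 40 women (*Sample size and power*) and the share d who do not sign. The article does not give d, so a range is assumed.

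Women with a count = 40 × (1 − d):

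- d = 10%: 36 with a count, 4 without
- d = 20%: 32 and 8
- d = 30%: 28 and 12
- d = 40%: 24 and 16

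Even at d = 10%, treating women as independent, the chance that at least one has no count is 1 − 0.9^40 = 0.985.

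**Step 3: can the restriction shift the between-arm difference?** Suppose that the workshop has no effect on the number of consultations. Suppose also that every woman who would sign in the arm with lower uptake would sign in the other arm too. Write L for the lower signing proportion, H for the higher, a for the mean count in women who sign under either arm, and m for the mean in women who sign only under the higher-uptake arm. Then:

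- mean among signers, lower-uptake arm = a
- mean among signers, higher-uptake arm = [L × a + (H − L) × m] / H

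All values below are assumed for illustration, with a = 1.3 throughout.

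| Control signing | Workshop signing | m | Control mean | Workshop mean | Workshop − control |
|---|---|---|---|---|---|
| 80% | 80% | any | 1.30 | 1.30 | 0 |
| 80% | 70% | 2.0 to 2.5 | 1.39 to 1.45 | 1.30 | −0.09 to −0.15 |
| 80% | 60% | 2.0 to 2.5 | 1.475 to 1.60 | 1.30 | −0.175 to −0.30 |
| 80% | 50% | 2.0 to 2.5 | 1.56 to 1.75 | 1.30 | −0.26 to −0.45 |
| 60% | 80% | 2.0 to 2.5 | 1.30 | 1.475 to 1.60 | +0.175 to +0.30 |
| any | any | 1.3 | 1.30 | 1.30 | 0 |

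Example, third row with m = 2.0: (0.6 × 1.3 + 0.2 × 2.0) / 0.8 = 1.18 / 0.8 = 1.475, and 1.30 − 1.475 = −0.175.

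The sign also depends on m. With 80% against 60% signing and m = 1.0, the control mean is (0.78 + 0.20) / 0.8 = 1.225 and the difference is +0.075. So a spurious difference is possible in either direction. It is zero when the same women sign in both arms, or when the extra signers have the same mean count as the others.

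**The case against.** A reader might infer that both measures are biased, that acceptability and workshop refinement rest wholly on women who chose surgery, and that decliners are barred from interview. The documents do not support this.

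- Every woman allocated to the workshop is asked for a written evaluation straight afterwards, whatever she later decides. The T1 measures, which include decision preference and choice, are taken about a week after the first consultation and do not depend on consent. Recruitment, retention, completion and adherence do not depend on it either. Refinement and acceptability therefore have other sources.
- The interviews are a purposive sample of five per arm for thematic analysis. There is no estimate to bias; the fault is a narrowed frame. As only 10 women are interviewed in any case, the Step 2 figures do not measure a loss of interviews.
- The interview sentence sets timing, not eligibility, and *Trial status* describes a purposive sample of volunteers without mentioning consent. This softens the reading. Still, a woman who never reaches the trigger is never due, and the wording works against the stated aim of variability.
- For the count, between-arm bias requires that the workshop changes who signs and that those women differ in their counts. Step 3 gives zero otherwise.
- The count is one of five service outcomes, is not a feasibility target, and will not be formally tested. Uptake is reported separately. All of that limits the impact, but none of it supplies a count for a woman who declines.
- A follow-up cut-off may well stand in the full protocol, so its absence from the article is not held against the plan.

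**Conclusion.** The point stands as a flaw in a stated definition that should be corrected; it does not threaten the pilot as a whole. As written, decliners, and deferrers until they sign, fall outside the interview frame and have no consultation count, against the plan's own treatment of reconstruction as an open choice.

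That conclusion rests on the text alone. Its size does not: the 4 to 16 women without a count assume that 10% to 40% do not sign, and the differences in Step 3 rest on assumed signing rates and mean counts. What can be said firmly is that the count describes signers only, and that the arms may not be comparable on it if the workshop alters who signs. The feasibility targets, the T1 measures and the post-workshop survey are untouched.

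**What to change.** Change the wording in both places and apply it to every randomized woman:

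1. Define a decision as made when surgical consent is signed or a decision against reconstruction is documented.
2. Record deferred or undecided as its own category, at one fixed time after the initial consultation. Deferral should not count as a decision made, because that would blur the proportion decided.
3. Report the number of consultations up to that time in all randomized women, by arm, next to the proportion decided.
4. Open the purposive interview sample to decliners and, at the fixed time, to undecided women, where such women exist and agree.

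The cost is a protocol edit, probably with a minor ethics amendment, and a chart check at the fixed time, which the article does not now describe. The number of interviews and visits stays the same. The drawbacks are that some interviews will be with women who have not yet decided, that places for decliners may go unfilled with five per arm, and that consultations to a fixed time is a slightly different quantity from consultations to a decision. *Trial status* places completion of the interviews after recruitment, so the frame could still have been widened at the date of the article.
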